## Abstract

**Background:**

Already a major health concern, late-life depression (LLD) is expected to form an increasing problem in the aging population. Moreover, despite current treatments, LLD is associated with a poor long-term prognosis and high rate of chronicity. Treatment provision and treatment accordingly warrant improvement, where add-on treatments might contribute to the efficacy of conventional therapies. Although it is known that impaired cognitive control contributes to LDD, it is not targeted sufficiently by current interventions. Research on cognitive control training (CCT) shows promising results on depressive symptoms, cognitive performance, and overall functioning. However, further research is needed to determine the long-term effects of CCT on LLD, its cost-effectiveness, and mechanisms of change.

**Methods:**

In the current multicenter randomized controlled trial (RCT) with a between-subjects design participants aged 60 years and over with a current LLD receiving treatment as usual (TAU) are randomized to add-on CCT or placebo training. Randomization is stratified by depression severity. Participants will receive eight online CCT or placebo sessions spread across four consecutive weeks. They will complete a post-training assessment after 1 month and three follow-up assessments scheduled three, six and 12 months after completing the training. We expect CCT and TAU to be more (cost-)effective in reducing depressive symptoms than placebo training and TAU. Additionally, we will be looking at secondary clinical, cognitive and global functioning outcomes and likely mechanisms of change (e.g., improved cognitive functioning, reduced rumination, and improved inhibition of negative stimuli).

**Discussion:**

The proposed RCT aims to contribute to the clinical and scientific knowledge on the long-term effects of CCT as an add-on treatment for LLD. Cost-effectiveness is particularly relevant considering the expected volume of the target demographic. The study will be a pragmatic trial with few inclusion restrictions, providing information on feasibility of web-based trainings in clinical settings. The outcomes are potentially generalizable to guidelines for treatment of LLD.

**Trial registration:**

This trial is registered in the Netherlands Trial Register (code: NL7639). Registered 3 april 2019.

## Background

Late-life depression (LLD), defined as major depressive disorder in individuals over 60 years of age, is a severe psychiatric illness, and has a prevalence ranging between 1 and 16% [20]. LLD has a poor long-term prognosis, and is associated with chronicity and high mortality [32, 34, 39]. Research shows that relapse, recurrence, and chronicity are higher in LLD than they are in younger populations [25], while in later life longer duration and chronicity are associated with further cognitive decline and somatic comorbidity such as cerebrovascular diseases and diabetes [2, 15, 47]. Due to aging of the global population, the burden associated with LLD is expected to increase further, which underscores the necessity of appropriate, evidence-based, and cost-effective treatments that are tailored to older populations [9].

Older adults with depression seem less responsive to standard treatment protocols than their younger counterparts. The Netherlands Study of Depression in Older Persons (NESDO) reported that only 18% of their participants diagnosed with major depressive disorder (MDD) had recovered after 2 years [15], despite having received psychopharmacological and psychotherapeutic treatment from primary or specialized mental health-care services. In comparison, approximately 80% of a younger adult population recovered in a two-year period [57]. Moreover, the efficacy of antidepressant medication is lower in older adults than it is in younger adults, which is possibly related to age-related cognitive impairments [4, 49]. For example, a meta-analysis of 74 studies showed that the number needed to treat for antidepressants was six for adults, eight for persons over 55 years and 21 for people over 65 years [59]. Furthermore, for older depressed patients access to therapy is limited [16] and treatment often does not take into account underlying age-specific contributing factors. Arguably, add-on treatments aimed at distinct mechanisms of LLD may improve outcomes in this population.

Impairment in a broad range of cognitive functions [51] is a common and disabling factor in LLD [42]. Apart from manifesting in performance tasks, cognitive deficits have also been observed in the brain. On a structural level, temporary changes in frontal brain regions are related to depressive symptomatology [1, 42] but particularly relevant are the changes discerned in the cognitive control network (CCN), which consists of the dorsolateral prefrontal cortex (DLPFC), the dorsal anterior cingulate cortex (dACC), and parietal regions [3]. The CCN plays a crucial role in emotion regulation and abnormalities in the associated regions can result in weakened cognitive control over negative affect [1, 3]. Cognitive control is implicated in a range of cognitive functions, such as working memory, attention span, and executive functions, loss of which can cause (increased) dysfunctional repetitive negative thinking, eliciting or aggravating depressive symptoms [18]. This specific vulnerability pathway has been supported by multiple MDD studies in adults, underscoring the importance of dedicated interventions targeting this crucial function [3, 8, 19]. Furthermore, in LLD the prevalence of impaired cognitive control functions is particularly high, which has also been associated with the reduced effectiveness of antidepressants [4, 42, 49]. An added treatment that specifically targets impaired cognitive control in older adults coping with depression may then be the preferred approach.

In recent years, researchers have started evaluating computerized cognitive control training (CCT) programs. These interventions generally consist of repetitive performance of cognitive tasks, aiming to (re)activate specific processes that potentially help restore the cognitive function addressed. In general, CCT is associated with small to moderate improvements of cognitive skills, depressive symptoms, and global functioning (see [35], and meta-analyses by Motter et al. [43]; Legemaat et al. [36]). These effects seem to complement the effects of treatment as usual (TAU). More specifically, CCT programs seem to be an effective and acceptable intervention for depressed older adults [43]. Additionally, online CCT is a low-cost, highly scalable treatment option. However, the number of studies examined was small and the authors did stress the need to further examine whether the cognitive gains spread to other neurocognitive processes, symptoms, and overall functioning. Relatedly, a systematic review of different types of CCT for healthy older participants shows that after training specific executive functions, small to moderate gains in cognitive performance are observed [45]. Interestingly, CCT appears especially effective when the applied tasks are continuously adapted to the participants’ performance level. Therefore, adding an adaptive form of CCT to current treatment of depressed older adults, might result in beneficial effects on cognitive functions, depressive symptoms and overall functioning. A randomized controlled trial (RCT) comparing such an adaptive CCT format to placebo add-on treatment in specialized health care would be the appropriate means to further test this.

The adaptive Paced Auditory Serial Addition Task (aPASAT) is a promising intervention aimed at enhancing cognitive control [24, 56]. In this task, individuals are instructed to sum up the last two numbers they heard in an auditorily presented continuous stream of numbers. It is adaptive in that its presentation speed is continuously matched to the participant’s performance, inducing greater emotional reactivity (e.g., frustration, negative thoughts, some negative affect), which might account for the benefits derived from such tailored tasks [11, 17]. Siegle et al. [56] concluded that the aPASAT activates the cognitive control network by showing that the dorsolateral prefrontal cortex is engaged during its performance. They also tested the task in participants with MDD, in whom the cognitive training reduced depressive symptoms and rumination more so than was the case in a control group receiving treatment as usual (TAU) [56]. Further studies continued to show beneficial effects of the aPASAT on depressive symptoms in various samples, where gains were possibly mediated by diminished rumination through improved cognitive functioning [12, 53, 60]. Interestingly, Brunoni et al. [12] observed, in a combined treatment group receiving CCT and transcranial direct-current stimulation, that sustained reduction in depressive symptoms was greatest in the older participants, even when controlling for changes in cognitive control throughout the training. This suggests that especially older depressed adults benefit from the aPASAT as an add-on to other treatment.

In summary, there is an urgent need for innovative, effective, and affordable treatments for LLD, which can be delivered alongside treatment as usual. The literature indicates that adaptive CCT approaches may be most effective in improving cognitive functioning and reducing rumination in older adults. The aPASAT is a relatively low-cost intervention that can be used as an add-on treatment to TAU, but large-scale clinical trials investigating its (cost-)effectiveness, working mechanisms, and feasibility in LLD are lacking. We aim to address these questions in the RCT described below.

### Aims and hypotheses

Our primary objective is to investigate whether the addition of a CCT program to ongoing LLD treatment (i.e., pharmacotherapy and/or psychotherapy) will help reduce depressive symptoms more so than a placebo training. Outcomes will be assessed 1 month post-training (T1) and during follow-up assessments at three (T2), six (T3) and 12 months (T4). We expect symptom reductions in the participants having received CCT to be greater than in the participants having completed the placebo training at all timepoints. Our second aim is to see whether CCT also exerts effects on other clinical measures including rumination (both trait and state), cognitive emotion regulation, working memory functioning (near and far transfer), inhibition, and quality of life. We expect that participants in the intervention group will show lower rumination, more adaptive cognitive emotion regulation, more improved working memory functioning, inhibition, and quality of life than the participants in the placebo group. Our third aim is to identify working mechanisms of CCT. We will examine whether improved working memory and reduced rumination mediate the effects of CCT on depressive symptoms, hypothesizing that improvements in depressive symptoms will follow improvement of working memory and reduction of rumination in the intervention group. Fourthly, we aim to study individual differences that could account for differences in the effect of CCT on symptom change, where we expect that baseline cognitive control, depression severity, and age will be moderating factors. Our fifth aim is to determine the cost-effectiveness of our add-on CCT, we will conduct a health-economic evaluation and budget-impact analysis, anticipating that CCT will reduce mental healthcare consumption during the follow-up period more so than placebo training. Finally, for our sixth aim, we will be assessing the acceptability and feasibility of the intervention by conducting qualitative interviews with subsamples of participants having received CCT, therapists involved in mental health care for older persons and other stakeholders to inform the further implementation of CCT as an add-on intervention next to existing treatments for LLD.

## Methods

### Design

Our study comprises a single blind RCT with a between-subjects design and two conditions. Participants are randomly allocated to the intervention condition (CCT) or the active control condition (placebo training). Qualitative interviews will be conducted in two subgroups of participants in the intervention arm.

### Participants

The study and control sample will both include adults aged 60 years and over with a current MDD diagnosis according to the DSM-IV (Diagnostic and Statistical Manual of Mental Disorders [5] receiving inpatient or outpatient treatment at three regional mental-health patient centers (Pro Persona, GGNet, and Senior Beter) or the Radboud University Medical Center, Nijmegen, the Netherlands, all specialized in the treatment of late-life depression. Depression diagnoses and exclusion criteria will be confirmed by trained clinicians using structured diagnostic interviews, either the Mini International Neuropsychiatric Interview (M.I.N.I.) [54] or the Structured Clinical Interview (SCID-I) [22]. Ongoing depression treatment can consist of a combination of pharmacotherapy, psychotherapy (e.g., cognitive-behavioral therapy or interpersonal psychotherapy) or psychosocial treatment, varying in frequency. Therapy can be adapted during the trial, with changes being documented by the researchers.

Exclusion criteria are:Any current (features of) psychotic disorder (according to the DSM-IV)A current (hypo)mania or a history of bipolar disorder (DSM-IV)A primary diagnosis of substance or alcohol dependence or abuse (DSM-IV)Acute suicidal risk, assessed by a trained clinicianInsufficient command of the Dutch language hindering participation in the study interventionSensorimotor disabilities that can interfere with task performance (computer-based CCT)Severe cognitive disabilities interfering with therapy / CCT participation as assessed by a clinician. In doubt, a Minimal Mental State Exam (MMSE) will be administered, where a score below 18 will serve as the threshold for exclusion [33]

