### Procedure

#### Recruitment, baseline assessment and randomization

A depression experience expert (author PO) provided input on the intervention and application procedure before the start of the trial. The recruitment and assessment process is illustrated in a flowchart shown in Fig. 1. Clinicians will provide eligible candidates with basic information about the study on paper and/or through an informative video. Clinicians will only inform patients capable of consenting to participation. Interested candidates are referred to the researchers who will provide further information by phone. Eligible participants will be asked to provide their written and informed consent for participation at their first visit to the treatment site, where they will subsequently complete the baseline assessment (T0) gauging depressive symptoms, cognitive functioning, rumination, cognitive emotion regulation, quality of life, and health-care consumption, and health-related disability (economic evaluation). If inclusion criteria are satisfied, participants are randomly assigned to the intervention (CCT) or the active control condition (placebo training) by computer-generated allocation stratified for depression severity as assessed with the Inventory of Depressive Symptomatology Self Report: mild (IDS-SR < 38), moderate (IDS 39–48) and severe (IDS > 49) [52]. At the end of the baseline assessment, all participants are provided with a digital tablet to enable them to complete the eight training sessions in their own homes. Researchers will explain, demonstrate and practice the use of the tablet and schedule the training sessions together with the participant. During the one-month training period, participants will receive email notifications to remind them of the task, while researchers will regularly contact them by phone to monitor their progress, with the number and timepoint of the telephone contacts being documented for each participant.

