**Fig. 1 Fig1:**
[figure not shown]
CONSORT flow chart

Approximately 1 month after the training, a post-training evaluation (T1) will be conducted including all but three of the baseline measurements. For an overview of the measurements and their timepoints, we refer to Table 1. Participants are asked whether any changes have occurred in the LLD treatment during the training period. Participants that did not complete all training sessions will also be asked to complete all post- and follow-up assessments.

**Table 1 Tab1:** Overview of measures and corresponding timepoints

Measure	Target concept	Baseline (T0)	Post-training (T1)	FU-1 (T2)	FU-2 (T3)	FU-3 (T4)
**IDS-SR**	Severity of depressive symptoms	●	●	●	●	●
**RRS**	Trait rumination	●	●			
**BFT**	State rumination	●	●			
**CERQ**	Cognitive emotion regulation strategies	●	●			
**PASAT**	Working memory capacity	●	●			
**RNG Task**	Working memory capacity	●	●			
**STROOP**	Inhibition of interfering stimuli	●	●			
**MOCA**	Cognitive dysfunction	●				
**EQ-5D-5l**	Health-related quality of life	●		●	●	●
**WHODAS 2.0**	Functioning and disability	●	●	●	●	●
**TiC-P**	Health-care costs (in the Netherlands) based on self-reported health consumption and productivity loss	●			●	●

*IDS-SR* Inventory of Depressive Symptomatology, *RRS* Ruminative Response Scale, *BFT* Breathing Focus Task, *CERQ* Cognitive Emotion Regulation Questionnaire, *PASAT* Paced Auditory Serial-Addition Task, *RNG task* Random Number Generation task, *Stroop task* (i.e. inhibition of interfering stimuli), *MOCA* Montreal Cognitive Assessment, *EQ-5D-5L* (i.e. quality of health), *WHODAS* World Health Organization Disability Assessment Schedule, *TiC-P* Trimbos Institute and iMTA Cost questionnaire for Psychiatry (i.e. economic costs)

Participants will again fill out the questionnaires 3, 6 and 12 months (T2, T3, and T4) post-training. Health-care utilization data will be collected with the TiC-P at T0, T3 and T4. The qualitative interviews for the flanking implementation study will be conducted between the post-training and 3-month follow-up. For a complete overview of the study design, we refer to Fig. 1.

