#### Economic evaluation

##### TiC-P

The Netherlands Institute of Mental Health and Addiction and iMTA Cost Questionnaire for Psychiatry [26] will be administered to assess healthcare utilization, patients’ out-of-pocket costs and productivity losses stemming from absenteeism and lesser productivity when working. The TiC-P is the most frequently used health service receipt questionnaire in the Netherlands. It will be administered at T0 and follow-up (T2, T3, and T4).

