#### Evaluation of clinical outcomes

All analyses will be conducted in agreement with the intention-to-treat (ITT) principle as per the CONSORT statement [40]. We will repeat the analyses in the per-protocol sample: participants who completed at least six training sessions. We will use two-level generalized mixed models on the longitudinal dataset to analyze the clinical outcomes over all 4 time points with condition, time and the interaction of condition x time as factors and the depended baseline measure as covariate while accounting for the multilevel data structure with participants being ‘nested’ in clinicians and assessments ‘nested’ within participants [27]. We will examine baseline cognitive control, depression severity, and age as possible moderators. We will examine the latter as possible moderating variable, because age was a relevant correlate for the effect of the aPASAT on depressive symptoms [12]. Rumination and working-memory functioning will be evaluated as potential mediators of change in depressive symptoms, for which Hayes’ PROCESS macro (in SPSS) will be used. These evaluations of the clinical outcomes will be carried out in SPSS [30] and Stata [58].

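### Setting and entry treatment vary widely but are absent from the strata and the IDS-SR model: the effect stays unbiased, at a modest cost in precision that baseline data could recover

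*Protocol article*

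**What the plan says.** All references are to the protocol article.

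- **Entry (Participants).** Patients are "receiving inpatient or outpatient treatment at three regional mental-health patient centers" or at the university medical center. Usual treatment is wide: "Ongoing depression treatment can consist of a combination of pharmacotherapy, psychotherapy (e.g., cognitive-behavioral therapy or interpersonal psychotherapy) or psychosocial treatment, varying in frequency". The article states no rule on how long treatment must have run or whether it must be stable.
- **Changes to usual treatment (Participants).** "Therapy can be adapted during the trial, with changes being documented by the researchers".
- **Allocation (Recruitment, baseline assessment and randomization).** Stratified by three IDS-SR severity bands and nothing else. Each participant receives a tablet "to enable them to complete the eight training sessions in their own homes".
- **Model (Evaluation of clinical outcomes).** The terms are "condition, time and the interaction of condition x time as factors and the depended baseline measure as covariate", with participants nested in clinicians. Setting and type of treatment are not terms.
- **What is asked about treatment change (Procedure, text after Fig. 1).** "Participants are asked whether any changes have occurred in the LLD treatment during the training period".
- **Care use.** The same Procedure text says: "Health-care utilization data will be collected with the TiC-P at T0, T3 and T4". Table 1 agrees. The TiC-P paragraph under Economic evaluation reads differently: "It will be administered at T0 and follow-up (T2, T3, and T4".

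**The concern.** Two patients with the same baseline IDS-SR can have different expected courses if one is an inpatient and the other an outpatient, or if one receives medication and the other psychotherapy. Neither the strata nor the model separates them beyond the baseline score and the clinician level. Predictable variation therefore stays in the residual, and a chance difference between arms in setting or entry treatment is not corrected. Setting is known at enrolment and care use is collected at T0, so the trial could use this information without new data collection.

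A second, smaller matter concerns follow-up. The article promises that therapy changes during the trial are documented. The one participant question it describes covers the training period only, and the two accounts of the TiC-P differ on whether care use is measured at T2. Aims and hypotheses expects less mental healthcare use in the CCT arm during follow-up, so the protocol itself anticipates that care will differ by arm after randomisation. Readers of the T2-T4 contrasts will want to see those changes.

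**Working it through.** **Inputs from Sample size calculation.** d = 0.45, two-sided alpha 0.05, power 0.80, correlation 0.50 throughout, mean cluster size 10, cv 0.475, icc 0.05, design effect 1.56, n = 33 per condition before and 52 after the design effect (104 in total).

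**1. Reproducing the plan's figure.** For a baseline-adjusted mean of r follow-ups with common correlation ρ:

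n per arm = 2 × (1.960 + 0.842)² / d² × f, where f = (1 + (r − 1)ρ)/r − ρ².

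- The first part, 2 × (1.960 + 0.842)² / 0.45², is 77.52.
- r = 3: f = 2/3 − 0.25 = 0.4167, giving 32.3, so 33. This matches.
- r = 4: f = 0.625 − 0.25 = 0.375, giving 29.07, so 30. This does not match. The text says four follow-ups but lists three times, and its figure fits three. Step 2 therefore uses three.
- Design effect: 1 + ((0.475² + 1) × 10 − 1) × 0.05 = 1.563. Then 33 × 1.56 = 51.5, so 52.

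**2. Effect of adding baseline covariates.** Let R² be the share of the variance left after baseline IDS-SR that setting and entry treatment explain. The documents give no value, so it is an assumption shown over a range. The standard error is multiplied by √(1 − R²), and the equivalent total sample is 104/(1 − R²). With effective n = 52/1.563 = 33.3 per arm:

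power = Φ( d × √(33.3/2) / √(f(1 − R²)) − 1.96 ).

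For r = 3 and R² = 0 the first term is 0.45 × 4.08 / 0.6455 = 2.84, so power = Φ(0.88) = 0.81. A single time point such as T4 has f = 1 − 0.25 = 0.75.

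| R² (assumed) | SE factor | Equivalent total n | Power, mean of 3 follow-ups | Power, one time point |
|---|---|---|---|---|
| 0 | 1.000 | 104 | 0.81 | 0.56 |
| 0.05 | 0.975 | 109 | 0.83 | 0.59 |
| 0.10 | 0.949 | 116 | 0.85 | 0.61 |
| 0.15 | 0.922 | 122 | 0.87 | 0.63 |

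These figures assume no dropout.

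**3. Chance imbalance.** For a yes/no entry factor with prevalence p and 52 per arm, the difference in prevalence between arms has standard deviation √(2p(1 − p)/52).

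- p = 0.20: 0.078, so a 95% range of ±15 percentage points.
- p = 0.50: 0.098, so ±19 percentage points.

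This is the loss in step 2 seen in a single realised trial. It should not be counted as an additional loss.

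**4. Clinician level.** If setting or treatment type largely follows the clinician, the nesting already takes up part of R². On the protocol's icc of 0.05 clinicians hold a small share of the variance, so it cannot absorb much. At the low end of the range, however, it could remove most of the gain.

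**5. Recording of treatment changes.** Set side by side, Participants covers changes during the whole trial, while the question described after Fig. 1 covers the training period. The TiC-P is given at T0, T3 and T4 in the Procedure text and Table 1, but also at T2 in its own paragraph. No section says how documented changes will be reported or used in the analysis of effect.

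**The case against.** The strongest reply is that nothing in the model is wrong. A baseline-adjusted mixed model under randomisation is valid, broad entry is deliberate in a trial described as pragmatic, and further covariates are often named in an analysis plan, which is not shown here. The assumed R² is not from the documents, the clinician level may take part of it, and the gain in power is a few points. All of this stands, and it limits the point to an improvement. It does not remove it: the article names its model terms explicitly, and the additional information is already collected at baseline.

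Four stronger readings are tempting, and the documents do not support them.

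- A reader might infer that changes in usual treatment go unrecorded after the training month. Participants says changes during the trial are documented, and the TiC-P records care use up to T4. Only the method of documenting later changes is undescribed.
- A reader might infer that mixed entry treatment biases or obscures the 12-month effect. Randomisation protects against bias. The cost is precision and uncorrected chance imbalance.
- A reader might want the model adjusted for later treatment changes. They arise after randomisation and CCT is expected to affect them, so adjustment could remove part of the effect or introduce bias.
- A reader might hope that a table of treatment changes by arm would separate a fading CCT effect from more intensive care in the placebo arm. It is descriptive and cannot do that alone.

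That patients may enter at any stage of treatment is likewise an inference from the absence of a stated rule.

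**Conclusion.** The point holds as a modest, inexpensive improvement to the primary model. Entry treatment and setting vary widely, and the strata and stated model use neither. The effect estimate remains unbiased. If these factors explain 5% to 10% of the residual IDS-SR variance, adjusting for them shortens the standard error by about 2.5% to 5% and moves power for the averaged effect from about 0.81 to 0.83-0.85. For a single late contrast it moves from about 0.56 to 0.59-0.61. The range rests on an assumed R², the protocol's correlation of 0.50, three follow-ups, no dropout and no absorption by the clinician level. A smaller true R², or overlap with clinician, would shrink the gain.

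The points on recording treatment changes, the TiC-P schedule and training at home are matters for reconciliation and do not alter the validity of the primary analysis.

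**What to change.** - **Evaluation of clinical outcomes.** Prespecify inpatient/outpatient status at T0 and entry treatment (for example medication yes/no and psychotherapy yes/no, from T0 records or the TiC-P) as baseline covariates in the IDS-SR model. State that the primary analysis stays intention-to-treat regardless of later changes in usual treatment, and that such changes are not covariates. Cost: wording and about three degrees of freedom with 104 participants.
- **Procedure and Participants.** Put the treatment-change question in the T2, T3 and T4 questionnaires, worded to cover the time since the previous assessment, so that the promised documentation spans the trial. Report changes by arm beside the T2-T4 contrasts, labelled as descriptive. Cost: one question in questionnaires already sent, and one table.
- **TiC-P.** Make the schedule the same in the Procedure text, Table 1 and the TiC-P paragraph.
- **Training location.** Reconcile the statement that all participants train at home with the inclusion of inpatients.
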